## Abstract

**Background:**

Major depression (MD) is a prevalent and disabling condition in Chile, with most cases being treated at the primary care level. In Chilean primary care, the authors have identified key factors associated with more complex presentations of MD and a poorer prognosis, such as a history of childhood trauma, suicidality, and comorbidities. These findings underscore the need for a multidimensional, trauma-informed, and interprofessional approach to the treatment of depression.

**Methods:**

This protocol is a two-arm, single-blinded, cluster RCT to compare the effectiveness of a collaborative multidimensional approach for depression (CMAD) versus usual care to treat MD in primary care clinics in Chile. In total, 394 depressed adults from 18 to 65 years of age in twelve clinics located in Chile’s Maule Region will be consented to participate in the study. Patients and care teams from each clinic will be randomized to the intervention or to the control arm.

Interprofessional teams in the intervention arm will attend 27 hours of didactic and active learning sessions focused on clinical competences to effectively engage, treat and follow up patients with the factors associated to the complex presentation of MD. Team in the control arm will receive 27 didactic sessions on current clinical guidelines for MD.

Patients of both arms will be blindly assessed at baseline, three months, and six months. The primary outcome will be the reduction in depressive symptoms, with secondary outcomes including improvements in anxiety symptoms, interpersonal and social functioning, and treatment adherence.

**Discussion:**

This protocol proposes the evaluation of an intervention designed to improve depression symptoms by enhancing the clinical competencies of primary care teams. These competencies are structured around collaborative care and trauma-informed practices.

**Trial registration:**

NCT05016388, registered on 16 August 2021 at
ClinicalTrials.gov.

AbbreviationsCMADCollaborative multidimensional approach for depressionGAD-7General Anxiety Disorder Scale-7GSESGeneral self-efficacy scaleERSEmotion regulation scaleMDMajor depressionMINIMini-International Neuro-psychiatric InterviewPHQ9Patient Health QuestionnaireOQ-45Outcome Questionnaire 45RCTRandomized controlled trialUCUsual Care

## Background

Depression is the leading cause of disability worldwide, contributing significantly to the overall global burden of morbidity and mortality.
^
1
^ It is estimated that it affects almost 280 million people worldwide.
^
1
^ In Chile, depression constitutes a significant public health problem.
^
2
^ Findings before the SARS-CoV-2 pandemic, showed that 18.2% of the adult Chilean population reported depressive symptoms, and 6.2% met the criteria for major depression (MD).
^
3
^
^,^
^
4
^ This prevalence increases with the pandemic.
^
5
^ Furthermore, it affects twice as many women as men, is the second leading cause of disability-adjusted life years and the first among women between 20 and 44 years.
^
2
^

Since 2001 there has been a Chilean national mental health program to treat MD. From 2006, this program has been known as Explicit Health Guarantees (Garantías Explícitas en Salud, GES, in Spanish), and is regulated by ministerial clinical guideline (Guía Clínica, 2013).
^
6
^ According to existing data, primary care treat 90% of MD cases.
^
7
^ Only those with current suicide attempts, suspected bipolarity or psychosis are referred to the specialty level.
^
2
^
^,^
^
7
^

Despite the implementation of the governmental guidelines, evidence shows limited competence in primary care teams to address MD,
^
7
^ with remission rates close to 50% at one year of follow-up.
^
8
^
^,^
^
9
^ This lack of remission is associated with a high prevalence of comorbid anxiety disorders, adverse childhood experiences, history of suicidality, and interpersonal difficulties.
^
10
^
^–^
^
12
^ These characteristics, which have been reported in refractory depression,
^
13
^ can be understood in light of the psychological and neurobiological sequel of exposure to adverse biographical experiences.
^
14
^ Currently, depression treatment guidelines lack specific recommendations to address these issues.
^
6
^

According to a consensus of international experts, the clinical characteristics of patients with refractory depression are better conceptualized as difficult-to-treat depression.
^
13
^ This conceptualization implies an understanding of depression as a chronic disease, which requires a collaborative, multidimensional, biopsychosocial clinical approach and an orientation to the management of symptoms and functional recovery.
^
13
^ Working with similar populations, others have proposed the adoption of trauma-informed care principles and approaches, considering the cumulative interactions between trauma exposure, socioeconomic disadvantage, depression and suicidality.
^
15
^
^,^
^
16
^

Both difficult-to-treat depression and trauma-informed care imply a collaborative organization health model similar to that proposed by Wagner
*et al* in the management of chronic diseases,
^
17
^ including anxiety and depressive disorders as proposed by Archer
*et al.*
^
18
^ It involves the presence of a case manager, a structured patient-centered approach, scheduled follow-up visits, the use of validated measures to monitor treatment response, and interprofessional communication between the different levels of care.
^
18
^

Considering all of the above, we hypothesize that a continuing education program for primary care teams that focuses on a bio-psychosocial, trauma-informed care approach implemented in a collaborative model will improve the outcomes of depression in comparison to usual care. Specifically, we hypothesize that the collaborative multidimensional approach for depression (CMAD) in primary care will demonstrate greater efficacy relative to usual care (UC) based on the clinical guidelines, considering:
1.Adult depressed patients in the CMAD arm significantly reduce depressive symptoms compared to the control group at 3 and 6 months after admission.2.Adult depressed patients in the CMAD arm significantly reduce anxiety symptoms compared to the control group at 3 and 6 months after admission.3.Adult depressed patients in the CMAD arm significantly reduce interpersonal dysfunction, social impairment, and emotional dysregulation compared to the control group at 3 and 6 months after admission4.Adult depressed patients in the CMAD arm achieve a significantly greater adherence than the control group at 3 and 6 months after admission.

The general aim of this study is to compare the effectiveness of a CMAD for MD versus UC on clinical and functional outcomes in a cluster randomized clinical trial (RCT) conducted in primary care clinics in the Maule Region of Chile.

The specific aims of this study are:
1.To compare changes in depressive symptoms between baseline and follow-up in adults treated for MD in primary care Maule clinics, using CMAD versus UC2.To compare changes in anxiety symptoms between baseline and follow-up in adult depressed patients treated for MD in primary care Maule clinics, using CMAD versus UC.3.To compare changes in symptoms of emotional regulation, interpersonal and social functions between baseline and follow-up in adult depressive patients treated for MD in primary care Maule clinics, using CMAD versus UC.4.To compare changes in therapeutic adherence between three and six months in adult depressive patients treated for MD in primary care Maule clinics, using CMAD versus UC.

## Methods

### Design

This study protocol is a cluster RCT with two parallel arms and single-blind outcome evaluation.

### Study setting

The Chilean healthcare system is divided into two main sectors: public and private. The public sector, managed by the National Health Fund (FONASA), covers 75% of the population, particularly those with lower incomes. Public healthcare services are provided through a network of health facilities, including hospitals and primary care centers. Primary care centers are a fundamental part of the Chilean public healthcare system and are primarily managed at the municipal level. Family health centers provide basic and preventive care, and services are free for patients.

To meet the objectives of this protocol, primary care clinics in the Maule Region, located in the municipalities of Talca, Curicó, Constitución, Sagrada Familia, Romeral, and Pelarco, are invited to participate. These centers represent both urban and rural areas in a disadvantaged region, where socioeconomic and educational levels are particularly low.
^
19
^ To obtain the sample, 12 centers are identified, and matched based on according to similar average socioeconomic and educational characteristics. Additionaly, the selection ensures that there is no cross-contamination between the patients in the control clinics and the intervention clinics.

The list of primary care clinics participating can be found at doi:
10.17632/jdftfbpvkn.1.

### Eligibility criteria

Adults between 18 and 65 years who enter treatment for depression in primary care clinics of the Maule Region are invited to participate in an evaluation after they sign a written informed consent statement.
^
34
^ Those with a confirmed diagnosis of MD, according to the Mini-international Neuro-psychiatric interview (MINI), are included in the study.
^
20
^ Exclusion criteria include the inability or unwillingness to sign informed consent, sensory disabilities, lack of access to a telephone, or referral to a specialist for conditions such as current suicidal attempts, bipolar disorder, or severe drug addiction.

### Sample size

The sample size estimation account for a 20% difference, as suggested by previous studies conducted in Chile.
^
21
^
^,^
^
22
^ This calculation is based on a one-sided model with an alpha of 5%, a power of 80%, a confidence level of 95%, and a maximum variance of 50%. A total of 240 depressed individuals are required, with 120 participants in each group (intervention and control). Bases on previous data, the intraclass correlation coefficient (ICC) is estimated to be 0.0337,
^
22
^ resulting in a design effect of 1.64 due to the involvement of 12 clinics. Applying this design effect increases the sample size to 341, based on a prior study the sample size is set at 394 patients.
^
8
^

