### Outcomes measures

**
*Primary outcome*
**

*Change in depressive symptoms*

Differences in depressive symptoms between baseline and follow-up across the two study arms are assessed at baseline, three months, and six months, as shown in the participants’ timeline (
Table 1), using the Patient Health Questionnaire validated in Chile. This questionnaire is a 9-item self-report survey that uses a 4-point Likert scale to screen for the presence of MD and monitor treatment effects. The total score ranges from 0 to 27, with higher scores indicating greater severity of depression. The presence of five or more symptoms on more than half of the days in the past two weeks suggests major depresson (
Table 1), using the Patient Health Questionnaire validated in Chile.
^
23
^ This questionnaire is a 9-item self-report survey that uses a 4-point Likert scale to screen for the presence of MD and monitor treatment effects. The total score ranges from 0 to 27, and a greater score means a greater severity of depression. The presence of five or more symptoms in at more than half the days in the last two weeks suggests MD.

**
*Secondary outcomes*
**

*Change in anxiety symptoms*

Difference in anxiety symptoms between baseline and follow up across the two arms of the study will be assessed at baseline and three and six months (
Table 1) by the Spanish validated version of the generalized anxiety disorder scale-7 (GAD-7).
^
24
^ The GAD-7 is a 7-item self-report survey that uses a 3-point Likert scale to screen for generalized anxiety disorder quantify symptom severity. The total score ranges from 0 to 21 points, and greater scores mean greater severity of anxiety.

*Change in interpersonal dysfunction and social role difficulties*

Difference in functional impairment in interpersonal and social areas between baseline and follow-up across the two arms of the study will be assessed at baseline, at three and at six months (
Table 1) by the subscales of the interpersonal functioning, and social role included in the Outcome Questionnaire 45 (OQ-45).
^
25

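### The printed 80% power is for a 20% difference, apparently in proportions, and does not describe the primary test, a linear regression of PHQ-9 scores at 3 and 6 months

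*Protocol article*

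**What the plan says.** The Sample size section of the protocol article states the target effect as a percentage: "The sample size estimation account for a 20% difference, as suggested by previous studies conducted in Chile". The remaining inputs are a "one-sided model with an alpha of 5%, a power of 80%, a confidence level of 95%, and a maximum variance of 50" percent. From these it derives a base size: "A total of 240 depressed individuals are required, with 120 participants in each group (intervention and control"). Clustering is added with two figures: "the intraclass correlation coefficient (ICC) is estimated to be 0.0337", "resulting in a design effect of 1.64 due to the involvement of 12 clinics". The total becomes 341 and is then set at 394. The section names no outcome, time point, mean difference or SD.

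Under Outcomes measures, the primary outcome is change in depressive symptoms on the PHQ-9, for which "The total score ranges from 0 to 27, with higher scores indicating greater severity of depression". The section also mentions a five-symptom threshold, but only to describe the instrument. No response or remission endpoint is listed among the primary, secondary or other outcomes.

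The first hypothesis, in the Background, is that patients in the intervention arm "significantly reduce depressive symptoms compared to the control group at 3 and 6 months after admission". The Data analysis section uses multivariable linear regression for differences at 3 and 6 months, with baseline adjustment. It names neither time as primary and does not say whether the test is one- or two-sided. The Study status section says that the study has concluded.

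**The concern.** A power statement means something only for the test that will be run. Here the inputs describe one kind of comparison and the primary analysis is another. Without a PHQ-9 difference and an SD, a reader cannot tell what change in score the trial was built to detect, or how to interpret a null result.

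Two further problems follow. The base size of 120 per group should follow from the printed inputs, so that the figure can be trusted. And a single 5%/80% pair is given for a hypothesis stated at two time points, so its error rate and power depend on whether success at one time is enough or both are needed.

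**Working it through.** **1. Reproducing the base size.** Inputs from the Sample size section: difference 0.20, one-sided 5% (z = 1.645), power 80% (z = 0.842). The maximum variance of 50% is read as p = 0.5 in each group, so p(1−p) = 0.25 per group and 0.5 for the two together. This reading is an inference.

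- One-sided: n per group = (1.645 + 0.842)² × 0.5 / 0.20² = 77.3, about 77.
- Two-sided: (1.960 + 0.842)² × 0.5 / 0.04 = 98.1, about 98.
- With the pooled-variance formula and rates of 0.5 and 0.3: 73 one-sided, 93 two-sided.
- With a continuity correction: 83 to 86 one-sided, 103 to 107 two-sided.

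None of these gives 120. About 119 appears only with inputs that the text does not state, such as two-sided 90% power for 0.6 against 0.8 with continuity correction. At 120 per group, one-sided power for a 20-point difference is Φ(0.20/√(0.5/120) − 1.645) = Φ(1.453) = 93%, not 80%.

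**2. The clustering step.** The design effect reproduces with 240/12 = 20 patients per clinic: 1 + 19 × 0.0337 = 1.64. The final size reproduces from 240: 240 × 1.64 = 393.6, so 394. The intermediate 341 does not, because 341/1.64 = 208. At the final size the clinics average 394/12 = 32.8 patients, and the design effect becomes 1 + 31.8 × 0.0337 = 2.07.

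**3. Power on the scale of the primary outcome.** The documents give no PHQ-9 difference or SD, so the stated 80% cannot be converted. What can be derived is the standardised difference that 394 patients detect with 80% power:

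| Effective N | Test | Detectable difference |
|---|---|---|
| 394/1.64 = 240 | one-sided 5%, normal | (1.645 + 0.842) × √(4/240) = 0.32 SD |
| 240 | two-sided 5%, normal | (1.960 + 0.842) × √(4/240) = 0.36 SD |
| 394/2.07 = 190 | two-sided 5%, normal | (1.960 + 0.842) × √(4/190) = 0.41 SD |
| 190 | two-sided 5%, noncentral t with 12 − 2 = 10 df | 0.45 SD |

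The last row allows for the small number of clinics. For an assumed PHQ-9 SD of 5, 6 or 7, 0.45 SD is 2.3, 2.7 or 3.2 points. An assumed 15% loss raises it to 0.47 SD. The planned baseline adjustment lowers it: with an assumed baseline–follow-up correlation r of 0.3 or 0.6, multiplying by √(1 − r²) gives about 0.43 or 0.36 SD.

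**4. Two time points.** Take each comparison at two-sided 5%, with test statistics correlated ρ.

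- If success at either time suffices, family error is 9.5% at ρ = 0.3, 9.1% at 0.5 and 8.3% at 0.7.
- If both must succeed, error stays at or below 5%. With 80% power for each, joint power is 64% if independent, 69% at ρ = 0.5 and 71% at ρ = 0.7.

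The stated 5% and 80% do not both hold under either rule.

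**The case against.** The case on the other side has real force in several places.

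- **Proportions is an inference.** This stands, and the point is worded accordingly. But if the 20% meant a relative change in mean score, power for the score still could not be derived, because no SD is given.
- **The 120 per group does no harm.** It exceeds what the stated inputs need, so the discrepancy is conservative. That stands; what remains is that the figure cannot be reproduced.
- **A success rule may sit in an analysis plan that is not shown.** This is fair, and the absence of a rule is not itself the finding. The finding is that the one power statement the article does print fits neither possible rule. Using six-month data for the ICC and the homogeneity check hints at six months but does not make it primary.
- **0.45 SD is not a figure from the documents.** Correct. It assumes a two-sided test, 10 df (open to debate, since clinics are pair-matched), the planning ICC carried over to PHQ-9 scores, and no gain from baseline adjustment.

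Two stronger readings are tempting and should not be made. A reader might infer that a one-sided 5% level contradicts 95% confidence, from "This calculation is based on a one-sided model with an alpha of 5%, a power of 80%, a confidence level of 95" percent. It does not: a one-sided 5% test pairs with a one-sided 95% bound, and the section mentions no two-sided interval. A reader might also infer that the trial runs at double the usual false-positive risk in the favourable direction. The one-sided choice appears only in the sample-size calculation, and the Data analysis section sets no sidedness, so the documents do not establish that.

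**Conclusion.** The point holds. The printed 80% power is for a percentage difference and is not tied to the PHQ-9 regression that is the primary analysis. On the binary reading, the base size is 120 against about 73 to 77 per group from the stated inputs (93 to 98 if two-sided). For the two time points, the cost is either a family error of about 8% to 9.5% or a joint power of about 64% to 71%. Which one applies depends on a rule that the article does not state.

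This is a fault in the power statement. It is not evidence that the trial is underpowered: across the assumptions above without loss to follow-up, 394 patients detect roughly 0.32 to 0.45 SD, which may be adequate.

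**What to change.** Restate the Sample size section as the PHQ-9 difference that 394 patients in 12 clinics can detect, and print the SD, ICC, sidedness and degrees of freedom used. On two-sided 5%, 10 df, ICC 0.0337 and no baseline adjustment this is about 0.45 SD; with adjustment it is smaller, and the assumed correlation should be given. Correct or explain the 120 per group.

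State that the primary test is two-sided at 5% with a 95% confidence interval. Then require both time points, adjust for two, or name one as primary. Because the study has concluded, that choice must be dated and disclosed as made after follow-up, not presented as prespecified.

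Keep the 20% calculation only if it is attached to a declared secondary PHQ-9 response or remission outcome, which can be derived from scores already collected.

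The change is to wording and needs no new data. The real cost is a possibly less favourable power statement and an openly post hoc rule for the two time points.

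### The 240 patients given as the requirement before clustering do not follow from the printed inputs, which give about 146 to 155; 240 may already contain the design effect

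*Protocol article*

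**What the plan says.** The Sample size section of the protocol article gives the effect first: "The sample size estimation account for a 20% difference, as suggested by previous studies conducted in Chile". It then gives the error rates and variance: "This calculation is based on a one-sided model with an alpha of 5"%, with "a power of 80%, a confidence level of 95%, and a maximum variance of 50"%. The result follows directly: "A total of 240 depressed individuals are required, with 120 participants in each group (intervention and control").

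Only after that does the section bring in an ICC of 0.0337, a design effect of 1.64 attributed to the 12 clinics, an increase to 341, and a final size of 394 attributed to a prior study. The Abstract repeats the 394. No loss allowance, continuity correction or other inflation is stated before the 240.

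**The concern.** The order of the paragraph makes 240 the individual-level requirement, with clustering added afterwards. A routine two-proportion calculation on the same inputs gives a much smaller number. If inputs and result disagree at this step, a reader cannot tell which difference, sidedness or power the trial was sized for. It is also unclear whether clustering was allowed for once or twice on the way to 394. The trial's result will be read against this statement of what it could detect, so the statement should be reproducible.

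**Working it through.** **Inputs, all from the Sample size section.** Difference 0.20, read as absolute. One-sided alpha 5% (z = 1.645). Power 80% (z = 0.842). "a maximum variance of 50"%, read as p = 0.5, so p(1-p) = 0.25 per arm. Equal groups. ICC 0.0337. Twelve clinics.

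**1. Attempt to reproduce 240 as an unclustered number.**

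- Maximum variance: n per group = 2 x 0.25 x (1.645 + 0.842)^2 / 0.20^2 = 77.3, so 154.6, or about 155 in total.
- 50% against 30%, pooled formula: n per group = [1.645 x sqrt(2 x 0.4 x 0.6) + 0.842 x sqrt(0.25 + 0.21)]^2 / 0.20^2 = 73.1, so about 146 in total.

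The printed 240 is 240/155 = 1.55 times the first and 240/146.3 = 1.64 times the second.

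**2. Variants.** These are also unclustered.

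| Variant | Total |
|---|---|
| One-sided, 80%, continuity correction | 166 to 172 |
| Two-sided, 80% | 186 to 198 |
| Two-sided, 80%, continuity correction | 206 to 214 |
| One-sided, 90% | 202 to 216 |
| Two-sided, 90% | 248 to 264 |
| 20% read as relative (50% against 40% or 60%), one-sided, 80% | 610 |

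None gives 240. Unclustered figures near 240 need inputs that are not printed. For example, two-sided 80% at 40% against 60% gives 194, and with 20% loss 194/0.80 = 243.

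**3. Does 240 already contain clustering?**

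- Patients per clinic at 240: 240/12 = 20.
- Design effect at that size: 1 + (20 - 1) x 0.0337 = 1.640, the printed value.
- The 50% against 30% figure times the design effect: 73.1 x 1.64 = 119.9 per group, or 240 in total. (If 73.1 is first rounded up to 74, the product is 121.4 per group.)
- The design effect applied to 240: 240 x 1.64 = 393.6, the printed 394.

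Both 120 per group and 394 therefore appear if clustering is applied once to reach 240 and again to reach 394.

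**4. The printed 341.** 341/1.64 = 208 and 341/240 = 1.42. Neither 146, 155 nor 240 leads to 341 through the printed design effect.

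**5. Clustering applied once.** With 12 clinics fixed, the design effect depends on the total N, so N = n0 x [1 + (N/12 - 1) x 0.0337], where n0 is the unclustered number. This solves to N = n0 x 0.9663 / (1 - n0 x 0.0337/12).

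- n0 = 146.3: N is about 240.
- n0 = 155: N is about 265.

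**6. Power, 20 points at maximum variance.**

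- 120 per group, clustering ignored: Phi(0.20/sqrt(0.5/120) - 1.645) = 92.7%.
- 240 in 12 clinics: effective N = 240/1.64 = 146, or 73.2 per group. Phi(0.20/sqrt(0.5/73.2) - 1.645) = 78% one-sided, and about 80% for 50% against 30%.
- 394 in 12 clinics: 394/12 = 32.8 per clinic. Design effect 1 + 31.8 x 0.0337 = 2.07. Effective N = 394/2.07 = 190, or 95 per group. Phi(0.20/sqrt(0.5/95) - 1.645) = 87% one-sided; with 1.960 in place of 1.645, 79% two-sided.

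**The case against.** The strongest reply is that the section's own figures do produce 120 per group, once the 20 points are taken as 50% against 30% and the printed 1.64 is included. On that reading 240 is a correct cluster-adjusted requirement in the wrong place, its power is about 80% as stated, and the final 394 exceeds it. This largely stands. It rules out saying that no reading of the inputs yields 120, and it changes the likely diagnosis from a wrong base number to a mislabelled one. It does not rescue the text: the article applies the design effect after 240, and its attribution of 394 to a prior study neither confirms nor excludes a second multiplication.

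Three stronger inferences are tempting and are not supported.

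- A reader might conclude that 120 per group really has 93% power. That holds only for individually randomised patients. Here clinics are randomised, and 240 patients in 12 clinics have about 78% to 80%.
- A reader might conclude that every later figure inherits a wrong base. The 1.64 and, numerically, the 394 are tied to 240, but 341 is not. Its mismatch is a separate problem.
- A reader might conclude that the trial is too small. The printed 240 is larger than its stated inputs need before clustering, and 394 is larger than the 240 to 265 needed after it.

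The practical consequence is also limited: the article reports that the study has concluded, so enrolment cannot change.

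**Conclusion.** The point holds as an error in the printed chain. As an unclustered requirement, 240 is about 1.55 to 1.64 times what its stated inputs give (about 155 or 146). The most economical explanation is that 240 is already adjusted for clustering and that the design effect was then applied a second time to reach 394. That remains an inference, because the text states the opposite order and 341 fits neither step. An undisclosed input, such as a two-sided test with a loss allowance, could also lie behind 240.

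The calculation assumes an absolute 20-point difference between proportions with p near 0.5; the relative reading gives 610 and is further from 240. The power figures at 394 assume equal clinic sizes and the printed ICC, allow for no attrition, and make no correction for having only 12 clusters.

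**What to change.** Rewrite the sample-size paragraph so that inputs and number agree, in one of two ways:

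1. Give about 146 to 155 as the unclustered number, naming the two proportions assumed, and carry it once through the design effect (about 240 to 265 in total for 12 clinics).
2. Keep 240 as an unclustered number and state the additional inputs that produce it.

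In either case, explain or remove 341. Keep 394 and print its cluster-adjusted power at about 32.8 patients per clinic: design effect about 2.07, effective N about 190, power about 87% one-sided or 79% two-sided for 20 points at maximum variance, with the caveats on attrition and number of clusters. Do not give the unclustered 93% as the power of 120 per group.

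The cost is one recalculation and a corrected paragraph, carried into the trial report. No patients, visits or analyses change.

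### The design effect of 1.64 applies to 20 patients per clinic; with 394 patients in the same 12 clinics it is 2.07, and the effective sample size is about 190

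*Protocol article*

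**What the plan says.** The Sample size section states that 240 patients are required, 120 per group, for a 20% difference with a one-sided 5% alpha, 80% power and maximum variance. It then says that "the intraclass correlation coefficient (ICC) is estimated to be 0.0337", "resulting in a design effect of 1.64 due to the involvement of 12 clinics". It goes on: "Applying this design effect increases the sample size to 341, based on a prior study the sample size is set at 394 patients".

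The number of clinics does not change anywhere. The abstract's Methods describe "394 depressed adults from 18 to 65 years of age in twelve clinics", and Study setting and Recruitment and randomization both give twelve clinics. The article states no cluster size, adds no clinics after inflation, and does not recompute the design effect for the larger sample.

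**The concern.** For a fixed ICC, the design effect depends on the number of patients per clinic. A planner can keep the clinic size at 20 and inflate by adding clinics, in which case 1.64 stays valid. A planner can instead keep the number of clinics and enlarge each one, in which case the factor has to be worked out at the larger size. The article holds the clinics at 12 but uses the factor for the smaller clinic size. Its ICC, design effect, clinic count and final sample size therefore cannot all hold together.

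The design effect is the main planning adjustment in a cluster trial. If it is understated, so is the variance inflation. Readers would credit the trial with more precision than 394 patients in 12 clinics provide, and a later trial could borrow a factor that does not belong to this design.

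**Working it through.** **Inputs** (all from Sample size; the clinic count also from the abstract and from Recruitment and randomization): required size 240; ICC 0.0337; design effect 1.64; printed inflated size 341; final size 394; 12 clinics.

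**Formula**, equal clinic sizes: DE = 1 + (m − 1) × ICC, where m is patients per clinic; effective size = N / DE.

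**Reproducing the article's figure.**
- m = 240/12 = 20, so DE = 1 + 19 × 0.0337 = 1.640. This matches.
- Backwards: m = 1 + 0.64/0.0337 = 19.99. No other clinic size gives 1.64.
- 240 × 1.64 = 393.6, which rounds up to 394. The printed 341 is not 240 × 1.64; it equals 208 × 1.64 = 341.1.

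**At the sizes the article prints.**

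| N | m = N/12 | DE | Effective size | Relative to 240 |
|---|---|---|---|---|
| 394 | 32.83 | 1 + 31.83 × 0.0337 = 2.073 | 394/2.073 = 190 | 79% |
| 341 | 28.42 | 1 + 27.42 × 0.0337 = 1.924 | 341/1.924 = 177 | 74% |

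**Unequal clinic sizes.** The article gives no distribution of clinic sizes. Using DE = 1 + ((1 + CV²)m − 1) × ICC with an assumed coefficient of variation of 0.3 to 0.6, the design effect at 394 is 2.17 to 2.47 and the effective size 181 to 159. The 2.07 is therefore the equal-size value.

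**Power at 190 effective patients (95 per arm), one-sided 5%.** The answer depends on what 240 stands for.

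- *Literal 20-point target, 60% v 40%.* Standard error = √[(0.6 × 0.4 + 0.4 × 0.6)/95.04] = 0.0711; 0.20/0.0711 = 2.814. Normal power = Φ(2.814 − 1.645) = 0.88. With a noncentral t on 12 − 2 = 10 degrees of freedom, for an unmatched clinic-level comparison, it is 0.83. Using the maximum variance of 0.25 in both arms lowers these to about 0.87 and 0.82.
- *Taking 240 as exactly the 80% requirement.* Noncentrality = (1.645 + 0.842) × √(190.1/240) = 2.213; power = Φ(2.213 − 1.645) = 0.71.

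These differ because 240 does not follow from its stated inputs. For a 20-point difference at maximum variance, 2 × 0.25 × (1.645 + 0.842)²/0.04 = 77.3 per arm, about 155 in total.

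**The case against.** **Attrition.** The strongest defence is that the printed numbers hide an attrition allowance. 341/1.64 is about 208, and 240/208 and 394/341 are both about 1.155. So the figures fit a base of 208 that becomes 240 and 394 after adding roughly 15%. The article does not say this, but a condensed article may leave such an allowance to the full protocol. If it is right, 240 is not the proper benchmark. The fault remains: 341 analysed patients in 12 clinics have a design effect of 1.92 and give 177 effective patients against 208, a shortfall of 15% rather than 21%.

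**Power.** A reader might infer that the trial is underpowered, at 71%. The documents do not support that as a finding. The figure treats 240 as exactly the 80% requirement, and 240 does not reproduce from its inputs. Under the literal one-sided target, 190 effective patients still exceed 80%. Moreover, the primary outcome is change in PHQ-9 score, analysed by linear regression adjusted for baseline, so neither calculation on proportions describes the planned analysis.

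**Attribution.** A reader might also infer that the article claims 394 clustered patients are worth 240 independent ones. It does not say so. It attributes 394 to a prior study, and the match with 240 × 1.64 is an inference from arithmetic.

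**Degrees of freedom.** Ten degrees of freedom assume an unmatched comparison. The clinics are matched in pairs, and six pairs would leave five degrees of freedom with an unknown gain from matching. The article names no reference distribution, so it cannot be said to have used a large-sample one.

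**Conclusion.** Wrong as written. The design effect of 1.64 belongs to 12 clinics of 20 patients. For the stated 394 in 12 clinics it is 2.07 and the effective size about 190, some 50 fewer than the 240 called required. At 341 it is 1.92 and about 177. These figures rest on the article's own ICC and clinic count and on equal clinic sizes; unequal sizes would normally make them worse.

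The effect on power is not settled. It is about 88% (normal) or 83% (t, 10 degrees of freedom, unmatched) for a literal 60% v 40% difference, and about 71% if 240 is the true 80% requirement. With clinics fixed at 12, an effective 240 would take about 712 patients: 240 × (1 − 0.0337)/(1 − 240 × 0.0337/12) = 711.4. That should not be read as a call for more enrolment. The literal target does not need 240, and Study status says the study has concluded.

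**What to change.** Rewrite the end of the Sample size paragraph without changing enrolment:

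- State that 394 patients in 12 clinics is about 33 per clinic, so that with ICC 0.0337 and equal clinic sizes the design effect is 2.07 and the effective sample size about 190.
- Give the power, or the detectable difference, that follows from that effective size, using a reference distribution suited to 12 clusters and saying whether the matching is taken into account.
- State the patients per clinic behind the design effect, in place of a reference to the clinic count alone.
- Recruitment is complete, so recompute the design effect and effective size from the actual clinic sizes and report those alongside.

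This takes a few sentences and one recalculation. It adds no patients and changes nothing in the conduct of the trial. The only cost is a less favourable stated precision.
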